#### Main statistical models

3.9.2

Mixed-effects models will serve as the core analytical framework to handle repeated measures collected at 1 day, 7 days, 4 weeks, and 24 weeks postoperatively. ① A linear mixed-effects model will be used for continuous outcomes, including gut microbiota indices (Shannon index, Bifidobacterium abundance), brain function parameters (fNIRS rCBF, EEG α-wave power), and biochemical markers (IL-6, TNF-α, 5-HT, and BDNF). ② A logistic mixed-effects model will be applied to binary outcomes, such as adverse events (SAE, skin allergy) and intestinal function recovery (first flatus within 48 h, first defecation within 72 h). ③ An ordinal logistic mixed-effects model will be used for ordinal outcomes, including scale scores (GIDS, HAMA, and HAMD).

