**Methods:**

This is a single-center, randomized, investigator-blinded, sham-controlled randomized controlled trial. A total of 50 patients aged 18–75 years with postoperative Stanford Type A or B AD will be enrolled and randomly assigned in a 1:1 ratio to either the active taVNS group or the sham control group. Both groups will receive standard postoperative care. The experimental group will additionally receive active taVNS targeting the vagus nerve-innervated auricular area (15 Hz, 200 μs pulse width), while the control group will receive sham stimulation at a non-vagus innervated site without electrical current. The intervention will be administered for 30 min, twice daily, over 7 consecutive days, with follow-up assessments continuing until 24 weeks post-surgery. Primary outcomes include changes in gut microbiota diversity/abundance and brain function (assessed via functional near-infrared spectroscopy). Secondary outcomes encompass inflammatory markers, plasma neurotransmitter levels, intestinal function recovery, and relevant psychometric scale scores. Safety will be monitored through vital signs, laboratory tests, and recording of any adverse events.

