**Figure 1 F1:**
[figure not shown]
Clinical trial flow chart.

**Table 1 T1:** Schedule of clinical trial index collection.

**Indicators**	**Screening period**	**Treatment period**			**Follow-up period**	
	**Visit 1 (days 1-7 before surgery)**	**Visit 2 (postoperative day 1, before intervention)**	**Visit 3 (daily monitoring for 1-7 days post-intervention)**	**Visit 4 (7 days post-intervention)**	**Visit 5 (4 weeks after surgery)**	**Visit 6 (24 weeks after surgery)**
General Information	✓					
Physical Examination	✓	✓	✓	✓	✓	✓
Written informed consent	✓					
Blood routine testduplicate	✓	✓		✓		
Liver function	✓	✓		✓		
Renal function	✓	✓		✓		
Coagulation function	✓	✓		✓		
Urine routine test	✓					
Urine pregnancy test in women of childbearing age	✓					
CTA of the Aorta	✓				✓	✓
Frequency of bowel sounds		✓	✓	✓		
The time of first flatus/defecation		✓	✓	✓		
GIDS		✓	✓	✓	✓	✓
HAMA		✓	✓	✓	✓	✓
HAMD		✓	✓	✓	✓	✓
SF-36		✓	✓	✓	✓	✓
PSQI		✓	✓	✓	✓	✓
IL-6		✓		✓	✓	✓
TNF-α		✓		✓	✓	✓
5-HT		✓		✓	✓	✓
BDNF		✓		✓	✓	✓
Gut Microbiota		✓		✓	✓	✓
BCI		✓		✓	✓	✓
NIRS		✓		✓	✓	✓
Adverse events	Record at any time					
Review of CRF	Review at any time					

GIDS, gastrointestinal dysfunction score in critically ill patients; HAMA, Hamilton anxiety scale; HAMD, Hamilton depression scale; SF-36, the short form 36 health survey; PSQI, Pittsburgh sleep quality index; IL-6, interleukin-6; TNF-α, tumor necrosis factor-α; 5-HT, 5-hydroxytryptamine; BDNF, brain-derived neurotrophic factor; BCI, brain-computer interface; NIRS, near infrared spectroscopy.

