### Sample size estimation

3.3

The sample size for this study was calculated using the standard formula for comparing means between two independent groups in a randomized controlled trial. The formula and parameters are defined as follows: Sample Size Calculation Formula:

$$\begin{array}{c} n=2\times {\left[\frac{\left(Z_{\alpha /2}+Z_{\beta /2}\times \sigma \right)}{\Delta }\right]}^{2} \end{array}$$
(1)

Where: *n* = sample size per group; *Z*_α_/2 = critical value for a two-tailed test at significance level α; *Z*_β_ = critical value for Type II error rate β; σ= population standard deviation of the primary outcome; Δ = minimum clinically important difference.

Basis for Parameter Setting: *Z*_α_/2: A two-tailed significance level (α) of 0.05 was used, corresponding to *Z*_α_/2 = 1.96; *Z*_β_: A statistical power (1 – β) of 80% was targeted (β = 0.2), corresponding to *Z*_β_ = 0.84; Δ and σ: Based on previous taVNS randomized controlled trials (17–19) and our pilot data, we assumed a continuous primary outcome (e.g., postoperative quality of life score or change in serum IL-6). The expected between-group difference (Δ) was three points, with a common standard deviation (σ) of five points.

Sample Size Calculation Result: Using the above parameters, 22 participants were required per group, yielding an initial total sample size of 44. Accounting for an anticipated 10% dropout rate, the final sample size was increased to 50 participants. These will be randomly assigned at a 1:1 ratio to the intervention (taVNS, *n* = 25) and control (sham stimulation, *n* = 25) groups.

Power analysis was performed for the primary outcomes (gut microbiota and brain function). The final sample size ensures ≥80% power for both. This sample size also covers the secondary endpoints and no separate calculation was needed.

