#### Intervention and follow-up period

3.5.3

All patients will receive standardized postoperative management, including nutritional support (standard liquid/semi-liquid diet) supervised by the hospital nutrition department. Concomitant medications affecting gut microbiota or motility will be documented. ① Intervention frequency: Twice daily, 30 min per session. ② Start time: Postoperative day 1. ③ Intervention course: 7 consecutive days. ④ Follow-up: Participants will be followed for 24 weeks, with periodic assessments of efficacy (e.g., inflammatory markers, gut microbiota, quality of life) and safety (e.g., adverse events, vital signs).

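### Section 3.9.2 gives the pre-treatment day-1 value no baseline role, and no single contrast is fixed for each primary indicator

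*Protocol article*

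**What the plan says.** Section 3.9.2 (Main statistical models) makes mixed-effects models the core analysis of "repeated measures collected at 1 day, 7 days, 4 weeks, and 24 weeks postoperatively". The linear version covers microbiota indices and brain function parameters, which are the primary outcomes.

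Table 1 heads the first of these visits "Visit 2 (postoperative day 1, before intervention" and schedules gut microbiota, BCI and NIRS there. Section 3.5.3 agrees on the order of events: "Start time: Postoperative day 1" and "Intervention course: 7 consecutive days". Follow-up then runs on: "Participants will be followed for 24 weeks".

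The next modelled visit is headed "Visit 4 (7 days post-intervention" in Table 1, whereas Section 3.9.2 counts it as 7 days after surgery.

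On the deciding comparison, the abstract says "Primary outcomes include changes in gut microbiota diversity/abundance and brain function" and names no visit. Section 3.6.1 lists metrics without a time point. Section 3.9.1 adds independent and paired t-tests and rank-sum tests, also without a visit, and sets a corrected alpha of 0.01 for five indicators. Section 3.3 sizes the trial with the "standard formula for comparing means between two independent groups".

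**The concern.** Two gaps meet in one sentence of Section 3.9.2.

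- **Day 1 has no stated role.** The expected arm difference at that visit is zero, because randomised patients have not yet been stimulated. Its use is to explain between-patient variation at later visits. Listed only as one of four repeated measures, it may not do that work, and under one possible test it would dilute the effect.
- **No contrast is fixed.** Four visits and two arms allow an average arm effect, a joint arm-by-visit test, or a difference at any one visit. Section 3.3 and the 0.01 level both assume that one of these has been chosen for each indicator.

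At stake are precision that could be had from data already being collected, and the validity of the multiplicity correction if the visit is settled after the data are seen.

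**Working it through.** **Inputs from the document.** Difference 3 points and SD 5 points, so 3/5 = 0.6 SD; two-sided alpha 0.05; 22 evaluable per arm (Section 3.3). Primary alpha 0.01 for five indicators (Section 3.9.1). Four visits (Section 3.9.2).

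**Assumptions.** Equal variance at each visit, compound symmetry with correlation ρ = 0.5 (range 0.3 to 0.7), normal approximation. The course of the effect after Visit 4 is not given, so it is varied.

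**The plan's own figure.** 2 × [5 × (1.96 + 0.84)/3]² = 43.6, i.e. 44 per arm, not 22; the 22 appears only if the factor 2 is dropped (21.8). That is a separate matter. I keep 22 because it is the plan's evaluable number.

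**Formula.** For a contrast with effect d and variance v (in SD units), SE = √(2v/22) and power = Φ(d/SE − 1.96), the opposite tail being negligible except where d is small.

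**One visit, Visit 4, d = 0.6**

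- Unadjusted: v = 1, SE 0.302, d/SE 1.99, power 51%.
- Simple change from day 1: v = 2(1 − ρ) = 1, power again 51%.
- Day 1 as covariate, or arm means constrained equal there: v = 1 − ρ² = 0.75, SE 0.261, d/SE 2.30, power 63% (55% to 80% for ρ from 0.3 to 0.7).

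**Averages, effect sustained at 0.6 from Visit 4 to week 24**

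- Four visits including day 1: d = (0 + 0.6 + 0.6 + 0.6)/4 = 0.45, a quarter lost. v = (1 + 3ρ)/4 = 0.625, SE 0.238, d/SE 1.89, power 47%.
- Three later visits, unadjusted: d = 0.6, v = (1 + 2ρ)/3 = 0.667, SE 0.246, d/SE 2.44, power 68%.
- Three later visits, baseline-adjusted: v = 0.667 − ρ² = 0.417, SE 0.195, d/SE 3.08, power 87% (85% to 95% over the range of ρ).

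**If the effect fades.** The adjusted Visit 4 contrast stays at 63%. For the adjusted three-visit average:

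- Half at week 4 and none at week 24: d = (0.6 + 0.3 + 0)/3 = 0.3, d/SE 1.54, power 34%.
- Effect at Visit 4 only: d = 0.2, d/SE 1.03, power 18%.

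**Multiplicity.** 0.05/5 = 0.01 allows exactly one test per indicator. Testing three post-baseline visits on five indicators makes 15 tests. At 0.01 each, the bound on the family-wise error is 15 × 0.01 = 0.15, and holding it at 0.05 would need 0.05/15 = 0.0033 per test.

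**The case against.** The strongest reply is that Section 3.9.2 only lists the data entering the model. Keeping a pre-treatment value in the response vector is ordinary practice, and constraining the arms to be equal at day 1 also keeps it there. The word changes in the abstract and the Table 1 label both hint that day 1 is meant as baseline. Model terms are commonly left to an analysis plan, and this is a condensed article.

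Much of this stands. A reader might infer that the plan tests an arm main effect averaged over four visits, and so averages the benefit of a 7-day course away. The document never says so, and it gives no basis for assuming that the effect fades. The dilution figures describe one possible test.

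A reader might also infer that Visit 4 must be the primary visit. The document does not support that either: the primary measures are repeated to week 24, so a sustained-effect contrast is equally defensible.

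Two things survive. Merely having day 1 in the response does not make it a baseline: with arm means left free at every visit, the Visit 4 difference is the unadjusted one (51%), and simple change from day 1 gives no more at correlation 0.5. And the article itself states a correction that allows one test per indicator without identifying that test, which is more than omitted model detail.

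**Conclusion.** The point holds in a limited form. Section 3.9.2 lists a pre-treatment value among the repeated measures without a baseline role, and nothing fixes the one contrast per primary indicator that Sections 3.3 and 3.9.1 presuppose.

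The firm part of the size is the gain from using day 1 as baseline: about 12 points of power at Visit 4 (51% to 63%) and, if the effect persists, about 19 points for the three-visit average (68% to 87%). The conditional part is that an arm effect averaged over all four visits would lose a quarter of a sustained effect and have 47% power. All power figures rest on 22 per arm, 0.6 SD, alpha 0.05, compound symmetry and a correlation of 0.5 that the document does not supply. The multiplicity consequence rests on none of the power assumptions; it arises only if more than one visit is tested or the visit is picked afterwards.

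This should be changed, but it does not show that the planned analysis is invalid.

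**What to change.** In Section 3.9.2, state that:

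1. Day 1 is the baseline, either as a covariate or with arm means constrained equal at that visit.
2. The outcome visits are Visit 4, week 4 and week 24, with arm, visit and arm-by-visit terms.
3. One contrast per primary indicator is fixed in advance, either the taVNS minus sham difference at Visit 4 or the average difference over the three post-baseline visits, and is tested once at the corrected level. The remaining contrasts are secondary.
4. The dating of Visit 4 is reconciled between Table 1 and Section 3.9.2, so that the contrast refers to one identifiable day.

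The cost is wording only, with no new data or visits. The choice in item 3 is a real trade-off. Like for like, with baseline adjustment, choosing Visit 4 gives up about 24 points of power if the effect persists (63% against 87%). Choosing the average costs more if the effect fades (34% or 18% against 63% in the two fading cases above). The sponsor should choose according to whether the claim is an end-of-course or a sustained effect.

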### Safety evaluation

3.7

Throughout the study, participants' vital signs will be continuously monitored, and laboratory investigations—including complete blood count, urinalysis, coagulation profile, and hepatic/renal function—will be performed. An Adverse Event (AE) is defined as any unfavorable medical occurrence following taVNS administration, irrespective of its causal relationship to the intervention. AEs may manifest as new symptoms, signs, diseases, or laboratory abnormalities. All AEs will be actively monitored, documented in the CRF, and assessed for their nature, severity (Grades 1–4), and relationship to taVNS (definitely, probably, possibly, or unrelated).

A SAE is defined as any AE that results in death, is life-threatening, necessitates hospitalization or prolongs existing hospitalization, results in significant disability or incapacity, or is a congenital anomaly. Any SAE must be reported to the Ethics Committee of Guangdong Provincial Hospital of Traditional Chinese Medicine within 24 h, accompanied by a completed SAE report form.

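### Section 3.9.2 assigns continuously recorded adverse events to a four-visit logistic mixed model that suits neither per-visit nor per-patient coding

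*Protocol article*

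**What the plan says.** Section 3.9.2 makes mixed models the core framework for "repeated measures collected at 1 day, 7 days, 4 weeks, and 24 weeks postoperatively". Its second item names the safety outcomes: "A logistic mixed-effects model will be applied to binary outcomes, such as adverse events (SAE, skin allergy"). The same sentence adds flatus and defecation thresholds, which each patient meets or misses once.

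Three other places describe the adverse event data:

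- Table 1 ties adverse events to no visit; the entry is "Record at any time".
- Table 1 heads the first post-surgical time point "Visit 2 (postoperative day 1, before intervention"), so it precedes any stimulation.
- Section 3.7 counts as an adverse event "any unfavorable medical occurrence following taVNS administration".

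Section 3.5.3 gives "Start time: Postoperative day 1" and a course of 7 days. Table 1 labels the next analysis time "Visit 4 (7 days post-intervention"), while section 3.9.2 counts 7 days from surgery. Section 3.9.1 has a general rule for categorical variables: frequencies, percentages and a chi-square test. The article gives no expected event rates, no rule for assigning an event to a visit, and does not say whether visit enters as a factor or as linear time.

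**The concern.** A repeated-measures model needs an outcome observed afresh at each time point. Adverse events accrue between visits, so someone must decide what a yes or no at a visit means. If it means an event since the previous visit, one of the four cells is empty by definition and the other three cover very different lengths of time. If each patient has a single yes or no, there is nothing repeated to model.

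Safety is one of the two stated aims in section 2. Under the stated model the safety report could contain time effects that mainly reflect the visit calendar, visit coefficients that do not settle, or an infinite odds ratio between arms. The treatment week, which matters most for a device applied to the skin, would also be pooled with about 23 weeks without stimulation.

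**Working it through.** The plan states no figure for adverse events, so there is none to reproduce. Visit days, course length and arm size come from the article; every event rate below is an assumption.

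**1. Windows under per-visit coding.** Visit days are 1, 7, 28 (4 weeks) and 168 (24 weeks). No stimulation precedes the day-1 visit, so its cell is zero. The others are 7 − 1 = 6, 28 − 7 = 21 and 168 − 28 = 140 days, or 3.6%, 12.6% and 83.8% of 167 days. If Visit 4 is a week after a course ending on day 7, it falls on about day 14 and the windows are 13, 14 and 140 days.

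**2. What window length alone does to a time effect.** Risk in a window of L days at constant hazard λ is 1 − exp(−λL), with λ = −ln(1 − R)/167 for an assumed 24-week risk R. Using the 6, 21 and 140-day windows:

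| Assumed R | 7-day window | 4-week window | 24-week window | OR, 24 weeks v 7 days | OR, 4 weeks v 7 days |
|---|---|---|---|---|---|
| 10% | 0.4% | 1.3% | 8.5% | 24 | 3.5 |
| 50% | 2.5% | 8.4% | 44.1% | 31 | 3.6 |

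Now assume a front-loaded hazard, 20 times the late rate to day 7 and 5 times to day 28. The weighted windows are 6 × 20 = 120, 21 × 5 = 105 and 140. With R = 20% the risks are 7.1%, 6.2% and 8.2%, and the odds ratios against the 7-day window are 1.2 (24 weeks) and 0.87 (4 weeks). The same calendar can therefore give a steep rise or almost none, and the model cannot separate length from hazard.

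**3. Skin reactions with visit as a factor.** Take 5 active and 2 sham events among 25 per arm, all in the 7-day window, and fit an illustrative logistic model without a random effect, with the 7-day visit as reference. The other visit coefficients are −9.75, −19.75 and −29.75 after 10, 20 and 30 iterations, with standard errors reaching about 600,000: they have no finite estimate. The arm effect stays finite. By hand it is ln[(5/20)/(2/23)] = ln 2.875 = 1.06, with SE √(1/5 + 1/20 + 1/2 + 1/23) = 0.89. That equals the fit on the 7-day visit alone, so the other three visits add nothing to it.

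**4. Once-per-patient coding.** With a single yes or no per patient, averaging over a random intercept leaves one event probability per arm. Any intercept variance reproduces those two probabilities, so the variance is not identified, and the patient-specific odds ratio depends on it.

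**5. Empty arms.** With 25 per arm and risk p in each, the chance that at least one arm has no event is 2(1 − p)²⁵ − (1 − p)⁵⁰.

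| Assumed p per arm | Chance that at least one arm has none |
|---|---|
| 2% | 84% |
| 5% | 48% |
| 10% | 14% |
| 20% | 0.8% |

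At 5% the sum is 2 × 0.277 − 0.077 = 0.478. Expected events per arm are 25p, which is 1.25 at 5% and 2.5 at 10%; such counts are too small for a chi-square test to be reliable.

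**The case against.** The strongest reply is that section 3.9.2 sorts outcomes by data type and never says that adverse events are coded at each visit. The flatus and defecation thresholds in the same sentence are once-per-patient outcomes, and an assignment rule is commonly left to the analysis plan. This is fair as far as the missing rule goes, and that absence is not the point here. The choice of model is stated in the article, and on the once-per-patient reading it fails for a different reason (step 4).

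The reply also disposes of several stronger readings:

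- *The whole time profile is fixed by the visit schedule.* Only the day-1 zero is. Later cells also depend on the hazard (step 2).
- *Unequal windows bias the arm comparison.* The windows are the same in both arms, so length alone does not.
- *Skin reactions separate completely and the model must fail.* The example shows quasi-complete separation on visit with a finite arm estimate. A late or persisting reaction is possible, and both arms wear electrodes (section 3.5.2). Separation by arm depends on rates the article does not give.

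Finally, section 3.9.1 already provides percentages and a chi-square test, and section 4 concedes low power for rare adverse events. Neither settles the matter: 3.9.2 names the mixed model for these events specifically, and chi-square is weak at these counts. It does stand that no method creates power here. Even 5 events against 0 gives a Fisher p of 0.050, so an interval will tell the reader more than a test.

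**Conclusion.** The point holds in limited form. The logistic mixed model in section 3.9.2 does not suit adverse events as Table 1 and section 3.7 define and collect them. Per visit, one cell is empty by definition, the others span 6 to 140 days (13 to 140 on the alternative reading of Visit 4), and visit coefficients for skin reactions are likely to be unstable. Per patient, the random effect has no data behind it.

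The size depends on assumptions. The odds ratios of 24 to 31 need a constant hazard and a 24-week risk of 10% to 50%; the diverging coefficients need visit as a factor and skin events confined to the treatment week; the 48% needs a 5% risk in each arm. The mismatch itself needs none of these. It affects the safety analysis, not the primary outcomes. A reader might infer that the safety comparison between arms is biased or cannot be estimated at all; the documents do not support that.

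**What to change.** Delete adverse events from the mixed-model list in section 3.9.2. State instead that, for each arm, the number and proportion of patients with at least one event will be reported, with a risk difference and exact confidence interval, using Fisher's exact test in place of chi-square for sparse counts. Do this separately for the treatment period and for follow-up, and add events per unit of patient-time wherever the periods are compared. Reconcile the two descriptions of Visit 4 so that the boundary between the periods is clear.

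The cost is a change of analysis wording; no data collection changes and the method is simpler. What is given up is a model-based time trend for adverse events.

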#### Handling missing data

3.9.3

The pattern of missing data will be first assessed using Little's test for Missing Completely at Random (MCAR). The mechanism will be classified as: ① MCAR: *P* > 0.05, indicating missingness is independent of both observed and unobserved data. ② Missing at Random (MAR): *P* < 0.05, but missingness is explainable by observed variables. ③ Missing Not at Random (MNAR): Missingness depends on unobserved data, as inferred from investigator notes and adverse event logs.

For data assumed to be MCAR or MAR, multiple imputation will be performed. The imputation model will include all outcome variables, baseline characteristics, and potential confounders. Predictive mean matching, logistic regression, and proportional-odds models will be used to impute continuous, binary, and ordinal data, respectively. Results from five imputed datasets will be pooled using Rubin's rules. For data suspected to be MNAR, a complete case analysis (CCA) will be the primary method, supplemented by sensitivity analyses to assess the robustness of the findings. Should the CCA and sensitivity analyses yield discrepant results, the potential impact of MNAR will be discussed as a study limitation. An interim review will be triggered if the missing rate for any outcome exceeds 30%, or if the rate for a key primary outcome surpasses 20%, to reassess data collection feasibility.

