#### Data collation

3.9.1

Data will be collected using CRFs, capturing baseline characteristics, intervention records, laboratory results, and scale scores. All biological specimens will be de-identified via unique codes to protect participant privacy. Statistical analyses will be performed using SPSS 22.0, with the following approach:

① Statistical Tests by Data Type: Categorical variables will be summarized as frequencies (percentages) and compared using the chi-square test. Continuous variables will be presented as mean ± standard deviation; after testing for normality and homogeneity of variance, parametric data will be analyzed using *t*-tests (independent or paired, as appropriate), while non-parametric data will be analyzed using the Mann–Whitney *U* test (rank-sum test). Ordinal data (e.g., scale scores) will also be analyzed using non-parametric rank-sum tests.

② Analysis of Primary and Secondary Outcomes: Outcomes include scale scores (GIDS, HAMA, HAMD, SF-36, and PSQI), brain function parameters (EEG, fNIRS-derived rCBF), gut microbiota metrics (diversity indices, taxon abundance), and biochemical markers (IL-6, TNF-α, 5-HT, and BDNF). A stratified multiple comparison adjustment will be applied: the primary outcome will use Bonferroni correction (corrected α = 0.01, accounting for five indicators), while secondary outcomes and biomarkers will use the False Discovery Rate (FDR) method (FDR = 0.05). Subgroup analyses (e.g., by gender, Stanford type) will also employ FDR correction to control Type I error inflation.

③ Correlation Analysis: Multiple linear regression will be used to explore associations between clinical outcomes, gut microbiota, inflammatory markers, and brain function.

④ Significance Level: A two-sided *P* value < 0.05 will be considered statistically significant for all tests, unless otherwise specified after multiplicity adjustment.

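### Five imputed datasets are too few for a 0.01 threshold: a primary result near it can change verdict with the imputation seed

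*Protocol article*

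**What the plan says.** Protocol article, section 3.9.3 (Handling missing data):

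- When imputation applies: "For data assumed to be MCAR or MAR, multiple imputation will be performed".
- How values are imputed: "Predictive mean matching, logistic regression, and proportional-odds models will be used to impute continuous, binary, and ordinal data, respectively".
- How many datasets: "Results from five imputed datasets will be pooled using Rubin's rules". The number is not a minimum and is not linked to the amount of missing data.
- When imputation does not apply: "For data suspected to be MNAR, a complete case analysis (CCA) will be the primary method".
- When missingness prompts a review: above 30% for any outcome, or "if the rate for a key primary outcome surpasses 20" per cent. The review concerns the feasibility of data collection, and nothing says that it changes the number of imputations.

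Section 3.9.1 (Data collation) sets the threshold for the primary outcome by Bonferroni: "corrected α = 0.01, accounting for five indicators". The unadjusted level is two-sided 0.05.

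Section 3.3 (Sample size estimation) plans 25 patients per arm and 10% dropout, and assumes a difference of 3 points with an SD of 5.

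**The concern.** The usual argument for five imputations concerns the efficiency of the point estimate. It does not address whether a p-value can be reproduced. With five datasets, the between-imputation variance is estimated on 4 degrees of freedom. That noise passes into the pooled standard error, the pooled degrees of freedom and the p-value, and a threshold of 0.01 lies in the tail, where such noise matters most.

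At stake is whether a primary outcome is declared positive. For a result near 0.01, two analysts who follow the plan exactly on the same data, with different seeds, could report opposite conclusions.

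**Working it through.** **Stated threshold.** 0.05 / 5 = 0.01, which reproduces the protocol's figure.

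**Efficiency of the point estimate.** With m imputations and a fraction of missing information (FMI) γ, relative efficiency is 1/(1 + γ/m). For m = 5:

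- γ = 0.10: 1/1.02 = 98%
- γ = 0.20: 1/1.04 = 96%
- γ = 0.30: 1/1.06 = 94%

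On this criterion five looks adequate.

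**Noise in the pooled result.** Scale the total variance to 1, with between-imputation variance B = γ and within-imputation variance W = 1 − γ.

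- The pooled estimate varies over seeds with SD √(B/m). At γ = 0.10 this is √(0.10/5) = 0.14 standard errors for m = 5 and √(0.10/50) = 0.045 for m = 50. At γ = 0.20 it is 0.20 and 0.063.
- The estimate of B varies as B·χ²(m−1)/(m−1), so its coefficient of variation is √(2/(m−1)): 0.71 for m = 5 and 0.20 for m = 50.

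**Effect on the p-value with the data held fixed.** Rubin's rules give T = W + (1 + 1/m)B and λ = (1 + 1/m)B/T. The Barnard-Rubin degrees of freedom are ν = ν₁ν₂/(ν₁ + ν₂), where ν₁ = (m−1)/λ² and ν₂ = [(ν₀+1)/(ν₀+3)]·ν₀·(1−λ), with ν₀ = 25 + 25 − 2 = 48. Each cell uses 100,000 draws. The documents give no FMI, so 0.05 to 0.30 is an assumed range.

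For data whose p-value with very many imputations would be 0.005:

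| FMI | 95% range of p, m = 5 | Chance p ≥ 0.01, m = 5 | m = 20 | m = 50 | 95% range of p, m = 50 |
|---|---|---|---|---|---|
| 0.05 | 0.0028-0.0104 | 3% | about 0 | about 0 | 0.0042-0.0061 |
| 0.10 | 0.0021-0.0169 | 14% | 0.3% | about 0 | 0.0038-0.0068 |
| 0.20 | 0.0012-0.0363 | 32% | 5.6% | 0.3% | 0.0032-0.0083 |
| 0.30 | 0.0006-0.0602 | 42% | 14% | 2.4% | 0.0027-0.0099 |

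For data whose many-imputation p-value would be 0.02, the chance that a seed gives p < 0.01 with m = 5 is 0.4% at FMI 0.05, 4% at 0.10 and 11% at 0.20. With m = 50 it is about 0 in all three.

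**How often this matters over trials.** The table conditions on a result near the threshold. For the overall rate, trials of 25 per arm were simulated at the protocol's effect, 3/5 = 0.6 SD. Assumptions: baseline correlation 0.5, values missing completely at random, imputation from arm and baseline only. The measure is the proportion of trials in which two seeds disagree on p < 0.01.

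| Missing | m = 5 | m = 50 |
|---|---|---|
| 10% (planned dropout) | about 8% | about 1-4% |
| 20% (review trigger) | about 13% | about 1-4% |

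A cross-check with predictive mean matching, the protocol's method for continuous outcomes, and effects of 0.6 and 0.85 SD gave 7-8% at 10% missing and 13-16% at 20% with m = 5, against about 2-5% with m = 50.

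**If the imputation model carries more information.** Adding one further correlated visit (assumed residual correlation 0.7, effect 0.6 SD) lowers the m = 5 rates to about 5% at 10% missing and 8% at 20%.

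**The case against.** The strongest reply is that five imputations give valid inference under Rubin's rules and lose only 2-6% efficiency. A trial is imputed once, and a clear result does not flip. At FMI 0.10, a many-imputation p of 0.03 falls below 0.01 for only 0.2% of seeds. The planned imputation model includes all outcomes, and there are several visits, so the missing information may be below the raw missing rate. All of this stands, and it keeps the point small. It does not remove the point, because near 0.01 the noise is still large enough to decide the verdict, and it can be avoided.

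The statistical analysis plan, which is not shown, might fix a seed, and leaving that detail to it is no fault. But a fixed seed makes the result repeatable without reducing the Monte Carlo error, and the number five is a choice that the protocol itself states.

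Three stronger readings are tempting, and the documents do not support them:

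- *The primary analysis is invalid, or its error rate is inflated.* Nothing here shows that. The fault is poor reproducibility near the threshold.
- *The verdict is close to a coin toss.* Counting a trial as unstable if any one of 12 seeds differs gives about 45% at 20% missing with m = 5. That count takes the worst of 12 runs, and it uses an effect of 0.9 SD, whereas section 3.3 implies 0.6 SD. It also leaves 12% at m = 50. The two-seed rate is the relevant one.
- *Up to 30% missing is tolerated on primary outcomes.* The 30% trigger is for any outcome. A key primary outcome is reviewed above 20%, so rates at 30% missing should not be used to size this point.

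**Conclusion.** The concern holds as a minor point that costs almost nothing to fix. With five imputations, a primary result near 0.01 can change verdict with the seed. The affected zone is roughly 0.005 to 0.02 at FMI 0.10 and wider at 0.20. Over trials at the protocol's effect, two seeds disagree in about 8% at the planned 10% missing and about 13% at 20%, against about 1-4% with 50 imputations.

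The rates rest on an assumed baseline correlation of 0.5, data missing completely at random, imputation from arm and baseline only, and a single comparison of the arms in place of the planned mixed model. They would be lower if the other outcomes are informative. The point does not arise where nothing is missing or where complete case analysis is used.

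**What to change.** In section 3.9.3, replace five with at least 50 imputed datasets, or with a rule that the number be large enough for the Monte Carlo error of the p-value to be negligible at 0.01. Fewer can suffice when little is missing: at FMI 0.10 and a many-imputation p of 0.005, 20 imputations already cut the chance of crossing to 0.3%, but at FMI 0.20 it is still 5.6%.

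No number removes the ambiguity of a result lying exactly on 0.01. More imputations narrow the zone in which the seed matters. Recording the seed in advance is sensible but secondary.

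The cost is computing time only. No patients, visits or clinical procedures change.
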